### Data management

An electronic CRF will be designed on the Research Manager (Clinical Trial Management Public Platform, Chengdu, China) clinical trials public management platform. A printed version will also be obtained. According to data management provisions, the electronic data will be saved for at least 30 years in the form of a CD.

The electronic CRF will be designed on the Research Manager clinical trials public management platform. The examination, input, and modification of case observation tables will be registered in a timely registered to ensure that the case observation tables are returned in a timely fashion and entered into the database. The original documents will be stored in the Department of Ophthalmology. The data administrator will be in charge of data entry. To guarantee the accuracy of the data, two data administrators will enter and check the data independently. In the case of questions arising from the CRFs, the data administrator will complete a data recheck query (DRQ) and issue an enquiry to the researchers through the clinical supervisor. The researchers will answer and return the DRQ as soon as possible. The data administrators will then revise, confirm, and enter the data according to the researcher’s reply and a DRQ will be issued again if necessary. All scientific research documents will be stored in special-purpose filing cabinets and locked to guarantee the security of the files stored. Custody of the files will be maintained through an on-the-spot inspection method. Personnel will be specifically assigned to manage the files. Various written materials will be saved according to needs. The information will be stored in a safe and orderly means to avoid water damage, staining, and crimping. The files will be kept clean and in good condition without damage. After the data is entered, lost or unreliable data will be subject to inquiry. Patients with multiple records will be inspected. The data will be validated by error analysis. Data management software will be used to build the database. Personnel will be specifically assigned to oversee the management of electronic data and organize the clinical research team in terms of data entry, verification, reporting, and answering questions.

### Harms

In the proposed study, adverse events, included bleeding, hematoma formation, fainting, severe pain, and local infection, will be reported
[26]. If adverse events occur during the observation period, details of these adverse effects will be recorded in the CRFs.

### Sample size and statistical analysis

#### Sample size

Based on the myopia diopter described in the literature
[27], the sample size will be estimated using the formula for superiority test sample size for two quantitative samples
[28]. The inspection significance level α = 0.05 (two-sided) with a combined standard deviation (S) of 0.25, will be obtained according to the literature, where *u*_1*-α*_, *u*_1-β_ are the bounds of the one-sided standard normal deviation, *u*_1–0.05_ = 1.645, and *u*_1-o.20_ = 0.845. *δ*_u_ is the effective boundary (*δ*_u_ >0), assuming *δ*_u_ = 0.2; θ is the estimate of the overall mean difference value of the acupuncture and control groups, and will be set at 3.0 according to the literature
[27]. By substitution into the above formula with n = 79 and an expected dropout rate of 20%, a total of 100 cases will be included. The sample ratio between the groups will be 1:1.

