### Statistical analysis

All statistical analyses will be performed using SPSS 17.0 statistics software. For quantitative data, the distribution pattern and homogeneity of variance will be examined. If there is a symmetric distribution, the mean (M) ± standard deviation will be used for statistical description, otherwise the M interquartile range (IQR) will be used to describe the trend of concentration and amount of scatter. If this condition is met, the Student's t-test will be used to compare the differences between the quantitative indices between the groups, otherwise the Wilcoxon rank-sum test will be used. For categorical data (binary classification and multiple classification), the composition ratio will be used for statistical description. Based on the observation of a theoretical frequency distribution, the χ^2^ or Fisher's exact test will be used, depending on the specific situation. The ranked data will be analyzed using the Wilcoxon rank-sum test.

Primary and secondary outcomes will be analyzed by the superiority test in accordance with the principle of intention-to-treat, using Per Protocol Set (PPS) and Full Analysis Set (FAS) datasets. The indices of safety evaluation will be analyzed using the Save Set (SS) dataset. The significance level in this study will be set at α = 0.05, and the one-sided test will be used. The detailed statistical analytical methods for primary and secondary outcomes and baseline data are shown in Table 
2 (variables, measures, and methods of analysis).

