**Table 2 Tab2:** **Variables, measures, and methods of analysis**

Variable/outcome	Hypothesis	Outcome measure	Methods of analysis
1) Primary	Intervention improved outcome from baseline to 7 days	Adherence% (>80%) [binary]	
Diopter	Diopter reduced or increased after treatment	Diopter [continuous]	t-test (rank-sum test) or repeated measurement
2) Secondary	Intervention improved outcome from baseline to 7 days	Adherence% (>80%) [binary]	
Visual acuity	Visual acuity did not increase or decrease after treatment	Visual acuity changes [continuous]	t-test (rank-sum test) or repeated measurement
Axial length	Axial length was not increased	Axial length changes [continuous]	t-test (rank-sum test) or repeated measurement
Lens thickness	Lens thickness was not increased	Lens thickness changes [continuous]	t-test (rank-sum test) or repeated measurement
Ciliary body thickness	Ciliary body thickness was not increased	Ciliary body thickness changes [continuous]	t-test (rank-sum test) or repeated measurement
Eye symptoms and systemic symptoms	No adverse symptoms	No adverse symptoms	Chi-squared test or Fisher’s exact test
Compliance	Compliance	Cure rate [binary]	Chi-squared test or Fisher’s exact test
Combination therapy/treatment	Improvement occurred	Whether other drugs were used during treatment [binary]	Chi-squared test or Fisher’s exact test
Adverse event	Improvement occurred	Presence of drug-related adverse event [binary]	Chi-squared test or Fisher’s exact test
3) Baseline analyses:		Adherence% (>80%) [continuous]	
Age		CRF [continuous]	t-test (rank-sum test)
Weight and height		CRF [continuous]	t-test (rank-sum test)
Female versus male		CRF [binary]	Chi-squared test or Fisher’s exact test
Race		CRF [more categories]	Chi-squared test or rank-sum test
Birth weight		CRF [continuous]	t-test (rank-sum test)
Preterm children		CRF [binary]	Chi-squared test or Fisher’s exact test
Parental myopia or not		CRF [binary]	Chi-squared test or Fisher’s exact test
Sibling myopia or not		CRF [binary]	Chi-squared test or Fisher’s exact test
Daily close reading time		CRF [continuous]	t-test (rank-sum test)
Outdoor time		CRF [continuous]	t-test (rank-sum test)
Eye exercises every day or not		CRF [binary]	Chi-squared test or Fisher’s exact test
Daily sleep time		CRF [continuous]	t-test (rank-sum test)
Room light conditions		CRF [binary]	Chi-squared test or Fisher’s exact test
Poor reading habits		CRF [more categories]	Chi-squared test or rank-sum test

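### The sample size is built on a 0.2 D superiority margin, but the analysis names standard tests with no margin, so the primary null is not the one used for sizing

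*Protocol article*

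**What the plan says.** The Sample size section says that "the sample size will be estimated using the formula for superiority test sample size for two quantitative samples". It gives a combined standard deviation of 0.25, normal quantiles of 1.645 and 0.845, an assumed overall mean difference θ printed as 3.0, and a further term δ, required to be positive and set at 0.2, which "is the effective boundary". The result is n = 79, raised to 100 in total for 20% dropout.

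The Statistical analysis section says that, when distributional conditions are met, Student's "t-test will be used to compare the differences between the quantitative indices between the groups", and otherwise the Wilcoxon rank-sum test. It adds: "Primary and secondary outcomes will be analyzed by the superiority test in accordance with the principle of intention-to-treat". On the error rate it says: "The significance level in this study will be set at α = 0.05, and the one-sided test will be used". It refers the reader to Table 2 for the detailed methods.

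For diopter, the primary outcome, Table 2 lists "t-test (rank-sum test) or repeated measurement". The hypothesis beside it is a change in either direction after treatment. The 0.2 boundary appears only in the Sample size section. Neither the analysis text nor Table 2 gives a margin, a shifted null or a confidence-limit rule.

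**The concern.** A superiority formula with a positive margin tests whether the difference exceeds that margin. A t-test or rank-sum test named without a null value is ordinarily a test of no difference. Table 2 uses the same test wording for baseline age, weight and reading time, where only a no-difference null makes sense.

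These are different success rules for the primary outcome. Applied as ordinarily understood, the named tests could label as superior a difference that the sizing treats as too small to count. The power calculation would then describe a test other than the one performed. If the matter is left open, the choice of null could be made after the results are known.

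**Working it through.** **Inputs.** From Sample size: S = 0.25, δ = 0.2 (taken as diopters, like the outcome), quantiles 1.645 and 0.845, 20% dropout. From Study design: 50 per arm, hence 40 per arm after 20% dropout. From Statistical analysis: one-sided 5%. Assumption: θ = 0.3, because the printed 3.0 does not reproduce the plan's figure.

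**1. Does the margin drive the plan's n?** The margin-superiority formula for two means is n per arm = 2·[(1.645 + 0.845)·S/(θ − δ)]².

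- Printed θ = 3.0: 2·(2.49 × 0.25/2.8)² = 0.10 per arm. The stated 79 is not reproduced.
- θ = 0.3 with the margin: 2·(2.49 × 0.25/0.1)² = 77.5 per arm, close to 79.
- θ = 0.3 without the margin: 2·(2.49 × 0.25/0.3)² = 8.6, so 9 per arm.

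Of these, only the calculation with θ = 0.3 and the margin comes near 79. The margin is therefore an active part of the sizing.

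**2. Decision thresholds for a t-test.** SE = S·√(2/n). The smallest significant observed difference is t·SE against zero and 0.2 + t·SE against the margin.

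| Per arm | SE | Level | t | Against zero | Against 0.2 |
|---|---|---|---|---|---|
| 50 | 0.0500 | one-sided 5% | 1.661 | 0.083 D | 0.283 D |
| 40 | 0.0559 | one-sided 5% | 1.665 | 0.093 D | 0.293 D |
| 50 | 0.0500 | two-sided 5% | 1.984 | 0.099 D | 0.299 D |
| 40 | 0.0559 | two-sided 5% | 1.991 | 0.111 D | 0.311 D |

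The two-sided rows are shown because Sample size gives "The inspection significance level α = 0.05 (two-sided) with a combined standard deviation (S) of 0.25", although its quantiles "are the bounds of the one-sided standard normal deviation". In every row the last two columns differ by exactly δ = 0.2, whatever the SD, sample size or sidedness.

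**3. How often the verdicts would differ.** Noncentral-t probabilities, 40 per arm, SD 0.25, one-sided 5%:

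- True difference 0.15 D, below the boundary: 84.5% success against zero, 0.6% against the margin.
- True difference 0.3 D (assumed): above 99% against zero, 55% against the margin. At 50 per arm the margin test has 63%.

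The 55% and 63% fall short of 80% because a figure that fits a per-arm requirement (77.5) was used as a total. That is a separate error. It is shown here only because it determines what keeping the margin would mean.

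**The case against.** The strongest reply is that no sentence says the test is against zero. The Statistical analysis section calls the primary analysis a superiority test, the same term that Sample size uses for its margin-based formula, and a t-test can be run against a null of 0.2. A rank-sum test can do the same if 0.2 is subtracted from one arm before ranking. This is also a journal article, and a null value or confidence-limit rule is often fixed in an analysis plan that is not shown.

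Much of this stands. A reader might infer that the protocol prescribes a test against zero, or that a rank-sum test cannot address a margin; the document supports neither. A reader might also infer that superiority could be declared at less than half the margin. That holds one-sided with SD 0.25 (0.083 and 0.093 D), but two-sided at 40 per arm the threshold is 0.111 D, or 56% of the margin. One-sided at 40 per arm, it reaches 0.100 D at an SD of about 0.27. Table 2 lists diopter rather than its change, so the relevant SD may not be 0.25.

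What does not stand is that this is only detail left for later. The protocol prints the tests and the hypothesis itself and presents Table 2 as the detailed methods. The Table 2 hypothesis is two-directional and has no margin, which conflicts with the sizing.

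**Conclusion.** The point holds as an internal contradiction. The sizing uses a null of at most 0.2 D. The printed analysis names standard tests and a no-margin hypothesis, and the term superiority test does not reconcile them. Under the one-sided 5% rule and SD 0.25, observed differences from about 0.08–0.09 D up to 0.28–0.29 D would pass an ordinary t-test of no difference and fail a test against the margin. The location of that range depends on SD, sidedness and evaluable numbers; its width of 0.2 D does not. These thresholds are for the t-test and do not transfer directly to the rank-sum test.

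The conclusion does not rest on θ = 0.3, which is needed only to explain 79 and to give power figures. Correcting the printed θ, the use of 79 as a total, or the one- versus two-sided level would each leave the primary null unresolved.

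**What to change.** State one null for the primary comparison in Sample size, Statistical analysis and Table 2.

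- **(a) Keep the margin.** Conclude superiority on diopter only if the lower one-sided 95% confidence limit of the between-arm difference exceeds 0.2 D, with the difference signed so that positive favors acupuncture. Any rank-based fallback must test the same 0.2 shift. Restate the power that 40 to 50 evaluable per arm gives: about 55% to 63% if θ is 0.3, an assumption.
- **(b) Test against zero.** Remove the margin from Sample size, restate the calculation and power, describe the claim as any difference, and report the confidence interval against 0.2 D.

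The printed θ of 3.0, the use of 79 as a total, and the conflict over one- versus two-sided alpha should be corrected in the same revision.

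Option (b) costs wording and a new calculation. Option (a) costs the same wording, but the sponsor must then accept the lower power or enlarge the trial: two arms of 79 with 20% dropout is 158/0.8 = 197.5, so 198 enrolled. The protocol article reports six participants recruited, so the choice is best made now.

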### Study design

This study will be a randomized, parallel, single-center, assessor- and statistician-blinded, controlled trial. The included subjects will be assigned to groups in a 1:1 ratio. The subjects (n = 100) will be randomly assigned to experimental (n = 50) and control groups (n = 50). The experiments began in January 2013 and will be completed in December 2014. The aim of this study is to objectively evaluate the clinical efficacy of acupuncture at five acupuncture points (bilateral Cuanzhu, Tongziliao, Sibai, Muchuang, and Hegu) in adolescent teenagers with mild-to-moderate myopia (Table 
1, Figure 
1). This report will be compiled according to the SPIRIT (Standard Protocol Items: Recommendations for Interventional Trials) 2013 Statement ‘*Defining Standard Protocol Items for Clinical Trials*’
[20].

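### The sample-size calculation does not reproduce: the printed inputs give about 1 child per group, and if θ was meant to be 0.3, n = 79 is a per-group figure used as the total

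*Protocol article*

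**What the plan says.** Every input and the result are in the section Sample size.

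- Error rate and spread: "The inspection significance level α = 0.05 (two-sided) with a combined standard deviation (S) of 0.25". The quantiles that follow, 1.645 and 0.845, "are the bounds of the one-sided standard normal deviation".
- Margin: δ_u "is the effective boundary", set at 0.2.
- Expected mean difference between acupuncture and control: θ "will be set at 3.0 according to the literature".
- Result: "with n = 79 and an expected dropout rate of 20%, a total of 100 cases will be included", at a 1:1 ratio.

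Study design confirms the group sizes: children are "randomly assigned to experimental (n = 50) and control groups (n = 50"). The section Randomization repeats 50 and 50.

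On the analysis, the section Statistical analysis states "Primary and secondary outcomes will be analyzed by the superiority test" and "The significance level in this study will be set at α = 0.05, and the one-sided test will be used". For diopter, Table 2 lists a t-test, a rank-sum test or a repeated-measures analysis. Neither place mentions the 0.2 margin.

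**The concern.** A reader should be able to put the printed inputs into the named formula and obtain 79. Here the answer is nearly three orders of magnitude smaller. The obvious repair, a slipped decimal point in θ, brings back a figure close to 79 but exposes a second problem: that figure counts one group, and the plan treats it as both groups together.

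What is at stake is the 80% power for the primary outcome. If θ = 0.3 was intended, the trial has about half the children that its own calculation asks for. A neutral result would then say little about whether acupuncture beats the margin.

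Two related points affect how the result is read. The sidedness of α is stated inconsistently. The margin that drives the sample size is not carried into the analysis section, so a reader cannot tell which observed difference would count as success.

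**Working it through.** **Inputs** (all from Sample size): S = 0.25; δ = 0.2; θ = 3.0; u(1−α) = 1.645; u(1−β) = 0.845, for 80% power; dropout 20%; ratio 1:1. The formula is not reproduced in the text at hand, so I use the standard one for two means with a superiority margin:

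n per group = 2 × (u(1−α) + u(1−β))² × S² / (θ − δ)²

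The numerator is 2 × 2.49² × 0.25² = 2 × 6.2001 × 0.0625 = 0.7750.

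**1. The plan's figure with its printed inputs.** θ − δ = 2.8, so n = 0.7750 / 7.84 = 0.099, which rounds up to 1 per group. Using θ alone or θ + δ as the difference, or two-sided α, still gives 1 per group. No reading with θ = 3.0 gives 79.

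**2. The value of θ that restores the figure.** With θ = 0.3, θ − δ = 0.1 and n = 0.7750 / 0.01 = 77.5 per group. By the noncentral t, 78 per group gives 80.0% power and 79 gives 80.5%. So 79 is recovered, as a number per group.

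**3. From n to the total.** 79 / 0.8 = 98.75, which the plan rounds to 100 in total. If 79 is per group, the total is 158 evaluable, and 158 / 0.8 = 197.5, or 198 randomised. For 79 to be a total (39.5 per group), θ − δ would have to be √(0.7750 / 39.5) = 0.14, so θ about 0.34. That value is not printed.

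**4. Power of 100 children, assuming θ = 0.3, margin 0.2 and pooled SD 0.25.** With 20% dropout, 40 per group remain, and SE = 0.25 × √(2/40) = 0.0559. Noncentral t:

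| Evaluable per group | One-sided 0.05 | Two-sided 0.05 |
|---|---|---|
| 40 (20% dropout) | 55% | 42% |
| 50 (no dropout) | 63% | 51% |

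**5. Dependence on θ** (40 per group, margin 0.2, one-sided 0.05):

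| θ | Power |
|---|---|
| 0.25 | 22% |
| 0.30 | 55% |
| 0.35 | 84% |
| 0.40 | 97% |
| 3.0 (as printed) | about 100% |

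**6. Sidedness.** Sample size calls α two-sided but uses 1.645, the one-sided 0.05 quantile. Statistical analysis specifies a one-sided test. With 1.96 in place of 1.645, step 2 gives 2 × 2.805² × 0.0625 / 0.01 = 98.35, or 99 per group.

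**7. Margin or zero.** With 40 per group at one-sided 0.05 the t quantile on 78 degrees of freedom is 1.665, and 1.665 × 0.0559 = 0.093. The observed difference needed is therefore about 0.09 D against zero and 0.2 + 0.093, about 0.29 D, against the margin. At θ = 0.3, power against zero exceeds 99.9%.

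**The case against.** **θ = 0.3 is inferred.** This stands. The document prints 3.0 and its source is not at hand. A reader might infer that the trial simply has 55% power. The documents support this only conditionally, because 0.3 was found by solving back from n, and power moves quickly with θ. The failure in step 1 needs no such assumption.

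**79 might be a valid total.** The formula cannot be seen, so neither its factor 2 nor its definition of n can be checked. If S² were the sum of the two group variances rather than a pooled variance, θ = 0.3 would give 6.2001 × 0.0625 / 0.01 = 38.75 per group, about 78 in total, and 40 per group would have about 80% power. A combined standard deviation most naturally means a pooled one, so this reading is less likely, but only the authors can exclude it. It does not rescue θ = 3.0.

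**Table 2 does not contradict the margin.** A reader might infer that naming a t-test means testing a difference of zero. That goes too far: a t-test can carry a shifted null, and the text speaks of a superiority test. What stands is that the analysis section does not repeat the margin.

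**A difference of 3.0 D might be called impossible.** It is 12 times the stated SD (3.0 / 0.25) and large beside an eligibility range of −0.5 to −6.00 D. The point does not need that judgement; the arithmetic is enough.

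**Power against zero is ample.** True at θ = 0.3, but the plan sized the trial against a margin. Moving to zero would change the primary hypothesis, so it is a choice and not a correction.

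**Conclusion.** The sample-size paragraph is wrong as written and has to be corrected. Its printed inputs give 1 child per group, not 79, without any further assumption about θ.

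The size of the shortfall is conditional. If θ was meant to be 0.3 and S is a pooled SD, 79 is a per-group number, the trial has about half the children its calculation requires, and power against the 0.2 D margin is about 55% at one-sided 0.05 after 20% dropout. If θ was about 0.34, the 80% would hold with 79 in total. The documents do not show which value was meant.

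The two-sided label on α contradicts both the quantile used and the analysis section. Whether the margin belongs to the primary test is left open. It is not a proven contradiction, but it moves the observed difference needed for success from about 0.09 D to about 0.29 D.

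**What to change.** 1. Check θ against the cited source and correct it. Show the formula and say whether S is pooled.
2. State whether n is per group or total, and carry that through the dropout step.
3. Reconcile the sidedness of α between Sample size and Statistical analysis.
4. Restate what 100 children deliver for the stated margin, as power or as a detectable difference. If θ is 0.3 and the test is one-sided, that is about 55% with 40 evaluable per group. With the plan's quantiles, 80% power corresponds to θ = 0.2 + 2.49 × 0.0559, about 0.34 D.
5. State in Statistical analysis and Table 2 whether the primary test is against the 0.2 D margin or against zero. That choice belongs to the investigators and should be fixed before unblinding.

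No extra enrolment is needed. The cost is a rewritten paragraph, a line in the analysis section and in Table 2, and probably a less favourable power statement. Trial status reports six children recruited, so the change comes early. A change to the analytical method must be notified as Protocol amendments and confidentiality requires: to the Ethics Committee, the subjects, the register and the publisher.
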